**Methods:**

The informatics system will be evaluated in a comparative effectiveness trial of 160 community-based primary care practices, cluster-randomized at the practice level. In the QUIT-PRIMO intervention, patients will be provided a paper information-prescription referral and then "e-referred" to the system. In the comparison group, patients will receive only the paper-based information-prescription referral with the website address. Once patients go to the website, they are subsequently randomized within practices to either a standard patient smoking cessation website or an augmented version with access to a tobacco treatment specialist online, motivational emails, and an online support group. We will compare intervention and control practice participation (referral rates) and patient participation (proportion referred who go to the website). We will then compare the effectiveness of the standard and augmented patient websites.

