## Methods

### Study design

We will recruit 160 primary care physician practices to our trial. As further detailed below, our primary intervention target is the clinical practices. Patients nested within these practices will be cluster-randomized to receive either a simple paper referral or the full intervention-a paper referral plus an "e-referral" (smoker's email will be entered into a referral system and the smoker will receive encouraging emails to participate). In addition to our primary cluster-randomized trial, patients who participate in the website will be further randomized (patient-level, within-practice randomization) to receive either a standard or augmented patient website. Thus, our design is a randomized trial of a patient smoking cessation intervention, nested within a cluster-randomized practice intervention.

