#### Decide2Quit.org, the patient-level intervention

Providers refer patients to Decide2Quit.org by paper prescription in the comparison group or by paper plus e-referral in the intervention group. Patients e-referred to Decide2Quit.org will receive reminder emails (two per week for four weeks) as cues to participation.

Patients who follow the referral and register with Decide2Quit.org will complete an online consent form and a baseline survey, including assessment of their readiness to quit smoking. This baseline data will be used to tailor the website to the individual.

Once registration is complete, smokers from both intervention and control practices will be further randomized. This within-practice randomization will allow smokers to receive one of two versions of Decide2Quit.org: a standard Decide2Quit.org or an augmented version of Decide2Quit.org (Table 1).

**Table 1 T1:** Major components of Decide2Quit.org

Component	Description
MyMail^a^	Receive messages from a tobacco treatment specialist

Our Advice^a^	Receive encouraging email messages from experts; messages tailored to stage of change

Your Online Community^a^	View messages and dialogue from smokers and ex-smokers through a resource website

My Health Risks^b^	Learn about specific health risks, including physical symptoms and harmful chemicals

Thinking About Quitting^b^	Helpful ideas and motivational recommendations (*e.g*., interactive calculators assessing triggers, decisional balance)

Family Tools^b^	How to get help from your family, deal with nagging, learn what kids think about smoking

Healthcare Provider Tools^b^	How to include your healthcare provider in your quit smoking plan

The Library^b^	Download articles and helpful tools about smoking cessation and smoking treatments

Web Resources^b^	Valuable additional websites for smokers

^a^These components are available only to the augmented Decide2Quit.org intervention; ^b^Standard components available to all smokers registered to Decide2Quit.org, both those randomized to standard version and those randomized to augmented version.

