Hypothesis 3 (Quit): The proportion of referred smokers who **Quit **at six months will be greater among those in the augmented Decide2Quit.org intervention compared with the standard intervention.

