### Outcomes

For our three hypotheses, we have three primary outcome variables (*i.e*., Refer, Go, Quit). For the primary analysis for hypothesis 1, the outcome will be the number of smokers referred from each group transformed into an average count per month by dividing the total by the length of time in months from the practice's first referral. As discussed above, in both arms, practices will use paper information prescriptions. The leave-behind part of the information prescription (see Appendix 1) will allow a consistent measure of referrals. In the QUIT-PRIMO intervention, the server will track the number of electronic referrals, allowing us to compare rates of referral based on paper and server in the intervention arm.

For hypothesis 2, our outcome will be the proportion of those referred who go to the website. Our interest in hypothesis 2, expressed as a proportion, will be the proportion of patients referred who log on, or "Go," to the website (% who go = number who visit/number referred). The number of smokers who visit will be recorded by the Decide2Quit system, linking each visitor to their primary care provider at initial registration. The number referred is continuously registered directly by the leave-behind referral receipts of the information prescriptions.

For hypothesis 3, we will define the outcome in two ways. In both approaches, the numerator will be the number of patients who report cessation at six-month follow-up calls. In our primary intent-to-treat analysis, the denominator will be all smokers who are referred (the same denominator used in hypothesis 2), estimating a population effect. This represents a conservative assessment since we assume that many patients will not go, and for the purposes of analyses, we will assume that these patients will not have quit. As a secondary analysis, we will assign the denominator as the number of patients who go to the website. For this secondary outcome, consistent with current guidelines for smoking cessation trials, we will assume that patients who are lost to follow-up, including those who go and do not agree to follow-up, are smokers [34].

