### Analysis

The mean number of referrals per month will be compared by study group using a two-sided *t*-test, employing Satterthwaite's approximation if the variances are substantially different. We will also examine the distribution of the referrals per month by study group and will use the two-sided Wilcoxon test if they appear non-Gaussian. We will assess the adequacy of randomization on characteristics of the practice that might influence referral rates. We will have data from an administrative database (size of practice, number of providers and staff) and provider reports of proportion of smokers in the practice. We will also conduct adjusted (using Poisson or negative binomial models based on distribution) analyses accounting for these factors.

For hypothesis 2, whether or not a patient goes will be considered a dichotomous outcome in a patient-level analysis. The main patient-level analysis will use a generalized linear model with a logit link to evaluate whether a referred smoker goes to the patient website. As this hypothesis represents a cluster-randomized trial, because each website links patients back to their practice, we will use generalized estimating equation (GEE) methods to account for clustering within practices.

For hypothesis 3, patients will be randomized within practices to standard Decide2Quit and augmented Decide2Quit. Because we are comparing rates in all instances between the standard Decide2Quit system and the augmented Decide2Quit, we will use a two-group chi-square test of equal proportions to test the statistical difference between the quit rates. We will next use a generalized linear model with a logit link to model tobacco cessation by treatment assignment adjusted for baseline readiness to change as entered into the website by the patient.

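### The primary denominator for hypothesis 3 (all referred smokers) is not defined by website arm, because the website version is randomised only at registration

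*Protocol article*

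**What the plan says.** Objectives, hypothesis 3, is a comparison of website versions. It concerns quitting as a share of those referred, which "at six months will be greater among those in the augmented Decide2Quit.org intervention compared with the standard intervention".

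Outcomes gives two denominators. The primary one reads: "In our primary intent-to-treat analysis, the denominator will be all smokers who are referred (the same denominator used in hypothesis 2"). For referred patients who never go to the site, "for the purposes of analyses, we will assume that these patients will not have quit". The other reads: "As a secondary analysis, we will assign the denominator as the number of patients who go to the website", with those lost to follow-up counted as smokers.

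Three places fix when the website version is assigned:

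- Abstract, Methods: "Once patients go to the website, they are subsequently randomized within practices".
- Study design: "patients who participate in the website will be further randomized (patient-level, within-practice randomization) to receive either a standard or augmented patient website".
- Decide2Quit.org, the patient-level intervention: "Once registration is complete, smokers from both intervention and control practices will be further randomized". Registration includes online consent and a baseline survey.

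Analysis tests hypothesis 3 with a two-group chi-square of standard against augmented, followed by a logit model "adjusted for baseline readiness to change as entered into the website by the patient". Sample size states the 10% cessation rate for patients randomised to the standard site and a detectable difference of 5 points.

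**The concern.** A two-group test of proportions needs one numerator and one denominator per group. Here the groups are website versions, and a person joins one only by registering. The primary denominator is fixed earlier, at referral, and takes in everyone who never reaches that step. Those people have no website assignment, and their outcome is assumed rather than observed.

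Hypothesis 3 is one of three primary hypotheses, and Sample size says it mainly drove power. If its denominator is not defined per arm, someone must choose later how to allot people who were never randomised, and the reported absolute effect depends on that choice. The intent-to-treat label is also attached to a set that was not randomised to the compared treatments, while the set that was randomised is called secondary.

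**Working it through.** **Inputs.** Sample size, Table 2: 3,000 visits, 22% smokers; 24% (intervention) and 12% (control) referred; 40% and 20% of those go. Sample size text: 10% cessation on the standard site and a 5-point difference, hence 15% on the augmented site. Study design: 160 practices. Assumed because not stated: 80 practices per arm, 1:1 website allocation, and everyone who goes registers and is randomised.

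**1. Reproduce Table 2.** 3,000 × 0.22 = 660 smokers. Referred: 660 × 0.24 = 158 and 660 × 0.12 = 79. Go: 158 × 0.40 = 63 and 79 × 0.20 = 16. All agree with the table.

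**2. Share of the primary denominator without a website arm.** Per pair of practices (one intervention, one control): referred 158 + 79 = 237; go 63 + 16 = 79; no arm 237 − 79 = 158; 158/237 = 67%. By practice arm: (158 − 63)/158 = 60% and (79 − 16)/79 = 80%.

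Over 80 + 80 practices: 80 × 237 = 18,960 referred; 80 × 79 = 6,320 randomised (3,160 per website arm); 12,640 with no arm. Sample size calls the flow yearly, while the Table 2 footnote spreads it over two years. On half the flow these totals halve, but the 67% does not change.

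**3. The effect under different treatments of non-goers.** Expected quits: 3,160 × 0.10 = 316 (standard) and 3,160 × 0.15 = 474 (augmented). Non-goers add nothing to the numerators.

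| Denominator | Standard | Augmented | Difference |
|---|---|---|---|
| Randomised patients | 316/3,160 = 10% | 474/3,160 = 15% | 5.0 points |
| Non-goers split evenly (6,320 each) | 316/9,480 = 3.3% | 474/9,480 = 5.0% | 1.7 points |
| Non-goers 45% standard, 55% augmented | 316/8,848 = 3.6% | 474/10,112 = 4.7% | 1.1 points |
| All referred used for both arms | 316/18,960 = 1.7% | 474/18,960 = 2.5% | 0.8 points |

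**4. The test under an even split.** z = (p1 − p2) / √[p(1 − p) × 2/n], with p the pooled rate. Take 686 randomised per arm, the number that gives 80% power for 10% versus 15% (two-sided 5% assumed).

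- Randomised: p = 0.125, n = 686, z = 0.05 / √(0.125 × 0.875 × 2/686) = 2.80.
- Even split: n = 3 × 686 = 2,058, p = 0.0417, z = 0.0167 / √(0.0417 × 0.9583 × 2/2,058) = 2.68.

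On the full flow the values are 6.01 and 5.74. The test barely moves; the absolute effect falls to a third.

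**5. Populations side by side.** The primary outcome uses referred smokers. The cessation rate in Sample size is stated among randomised patients, which is the secondary set. The Sample size figure and the primary outcome therefore describe different populations.

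**The case against.** The best defence is that the protocol names its aim, a population effect, and fixes the outcome of non-goers as not quit. Only their attribution to an arm is missing. Splitting them in the allocation ratio would supply it, leave the relative effect unchanged (3.3/5.0 = 10/15) and barely alter the test. Both definitions would be reported, so the 5-point contrast would be seen as well. Counting non-goers as smokers does lower the absolute rates, which is the sense of conservative that the protocol explains. An analysis plan that is not shown might contain the split.

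Most of this stands, and it limits the point. It does not rescue the primary label. A split, wherever it is written down, assigns people to arms by convention and not by randomisation, so the result is still not intention-to-treat for the website comparison.

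Three stronger readings are tempting, and the document does not support them:

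- That the primary comparison cannot be computed at all. It can, once a split is chosen; the defect is that none is given and any choice is artificial.
- That the readiness-adjusted model cannot run. Only registrants have the covariate, but Analysis does not tie that model to the referred denominator, and it is feasible among those who go.
- That quits per referred smoker should be tested between e-referral and paper practices instead. Hypothesis 3 contains no such comparison. Referral also follows practice randomisation and is expected to differ by arm (24% versus 12% in Table 2), so the groups compared would be selected by the intervention.

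**Conclusion.** The point holds. As written, the primary denominator for hypothesis 3 has no value per website arm. At planning rates 67% of it (60% in intervention and 80% in control practices) belongs to neither arm. The share depends on the planned go rates and equal numbers of practices per arm, but the defect exists at any go rate below 100%. If some who go do not complete registration, the share without an arm is larger.

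The consequence lies in the estimate and its label more than in the p-value. The planned 5-point difference becomes about 1.7 points under an even split, and 0.8 or 1.1 under the other two treatments shown. No data are lost, and the sound analysis is already planned, but as secondary. The correction matters because this is a declared primary outcome.

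**What to change.** In Outcomes, define the primary hypothesis 3 population as all patients randomised to standard or augmented Decide2Quit.org at registration, analysed as assigned, with those lost to follow-up (including those who decline it) counted as smokers. This is the present secondary definition, stated in terms of randomisation rather than visiting. In Objectives, replace referred smokers by randomised registrants in hypothesis 3. In Analysis, say that the chi-square test uses this population.

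Quits per referred smoker may still be reported descriptively, without a test between website arms and without the intent-to-treat label.

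The cost is wording in three sections. No new data, patients or follow-up are needed, and the primary outcome then matches the population for which Sample size states its cessation rate.

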### Sample size

We calculated sample size for each of our three hypotheses. Power was primarily driven by hypothesis 3 (six-month cessation). We first estimated the number of smokers per practice that will participate in the website over time. The average patient panel of a primary care provider is approximately 2,300, although not all are seen in a given year. We estimated 1,500 visits per year. Based on tobacco use prevalence, approximately 22% of the patients will be smokers. To be conservative, we assume that we will have only two providers per practice actively participating in the intervention. Using these numbers, we have estimated the number that will participate per practice yearly (Table 2). We expect 158 referrals from each intervention practice and 79 from each control practice. Based on these samples, and assuming a cessation rate of 10% among patients randomized to the standard Decide2Quit.org, we have 80% power to detect a 5% difference in cessation, comparing the standard and augmented Decide2Quit.org.

**Table 2 T2:** Flow of 3,000^a ^patients through the intervention--Refer → Go → Quit

	Intervention		Control	
**Start with 3,000 patient visits**	**Percent**	**Resulting N**	**Percent**	**Resulting N**

Smokers	22%	660	22%	660

Smokers **REFER**red	24%	158	12%	79

Smokers referred who **GO**	40%	63	20%	16

Smokers that go who **QUIT**	15%	10	10%	2

^a^3,000 patient visits (1,500 per year over two years).

### Blinding (masking)

Because each practice is informed, they will be provided tools aimed at enhancing referral, and since specifics of either arm are not described at any time, the practice is blind to group assignment. During the training process up to the point of randomization, the study coordinator is blind to which arm the practice will be assigned; however, they are unblinded once randomization occurs in order to provide direction for the appropriate referral process. Each study coordinator is trained to minimize any bias in communication with the implementation coordinators based on which arm they are assigned. Practices remain blind. In turn, all patients are blind to website characteristics and which randomized group they will be assigned to. Patients remain blind until completion of the study. At completion of the study, all practices and patients are unblinded and given the opportunity to utilize all features of both websites.

### Analysis

The mean number of referrals per month will be compared by study group using a two-sided *t*-test, employing Satterthwaite's approximation if the variances are substantially different. We will also examine the distribution of the referrals per month by study group and will use the two-sided Wilcoxon test if they appear non-Gaussian. We will assess the adequacy of randomization on characteristics of the practice that might influence referral rates. We will have data from an administrative database (size of practice, number of providers and staff) and provider reports of proportion of smokers in the practice. We will also conduct adjusted (using Poisson or negative binomial models based on distribution) analyses accounting for these factors.

For hypothesis 2, whether or not a patient goes will be considered a dichotomous outcome in a patient-level analysis. The main patient-level analysis will use a generalized linear model with a logit link to evaluate whether a referred smoker goes to the patient website. As this hypothesis represents a cluster-randomized trial, because each website links patients back to their practice, we will use generalized estimating equation (GEE) methods to account for clustering within practices.

For hypothesis 3, patients will be randomized within practices to standard Decide2Quit and augmented Decide2Quit. Because we are comparing rates in all instances between the standard Decide2Quit system and the augmented Decide2Quit, we will use a two-group chi-square test of equal proportions to test the statistical difference between the quit rates. We will next use a generalized linear model with a logit link to model tobacco cessation by treatment assignment adjusted for baseline readiness to change as entered into the website by the patient.

## Discussion

Despite some success in targeting one aspect or another of health services, single-dimension provider or patient implementation strategies are inherently limited. Using the Internet as a delivery method provides the potential to link multiple provider and patient intervention components, but this potential has not yet been realized. Our goal is to link providers and patients through an innovative electronic system with redundant cues and reminders to encourage participation at all levels of the clinical microsystem. Within the intervention group, the system will provide the practices with feedback and the patients with encouragement.

Once referred, the patient system has been developed to include current innovations in online smoking cessation interventions. Standard components include educational materials, interactive decision support tools (*e.g*., "What do I have to overcome?"-an assessment of triggers to smoking), and a quit plan tailored to readiness to quit. Additional, more innovative components, including online counseling with a tobacco treatment specialist through an asynchronous secure messaging system, are available in the augmented Decide2Quit.org. Our goal is to analyze the impact of this integrated system in terms of process (Refer and Go) and outcomes (six-month smoking cessation).
